### Outcomes

Descriptive statistics will be generated to describe the data. Mean comparisons will be used to test the hypothesis that participants in the marketing condition will have greater perceptions of service (as measured by the PSQ). The hypotheses that participants will report greater behavioral intentions to use EBP and will demonstrate greater likelihood to request information about EBP will be measured by group comparisons using continuous ratings on the Behavioral Intentions Scale and a categorical indicator of whether the participant actually requested information, respectively. If group differences emerge in these basic analyses, multiple regression models will test whether the group differences persist when controlling for pre-manipulation variables such as EBP attitudes, EBP awareness, intentions to seek therapy, and readability statistics generated on the messages. For all of the hypotheses, exploratory analyses will be conducted to evaluate potential moderators and mediators. Ethnicity/race, gender, and treatment history will be tested as potential moderators of group differences, and ratings of the information (e.g., ease of understanding, believability) will be tested as potential mediators of outcome. In addition, for the hypotheses about behavioral indicators (e.g., Behavioral Intentions Scales and likelihood of requesting information), PSQ ratings will be examined as potential mediators of outcome. These analyses will be conducted to observe trends and highlight directions for further research.

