### Sample size and power

One meta-analysis of the effect size (ES) of marketing campaigns on the proportion of customers inquiring about or purchasing a service found an average ES of .20 across 133 studies [80]. Of note, only one of the 133 studies tested marketing for a health-care service, and this study found a higher ES of .30. This ES is consistent with results of a recent quasi-experimental study comparing the effectiveness of a DTC campaign versus standard clinical guidelines in predicting cervical cancer screenings (d = .26) [81]. Assuming that awareness of the services marketed in prior studies was higher than current awareness of EBP, targeted marketing has the potential to produce larger ES in the current study. The target sample of 160 (n = 80 per group) will provide 71 percent power to detect an ES of .4; 88 percent for an ES of .5; and 96 percent for an ES of .6 [82]. Thus, the proposed sample size will be adequate to detect a medium ES, which is appropriate for a study that aims to provide proof of concept.

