### Randomization

A computer-generated urn randomization procedure will be used to retain random allocation, while balancing relative probabilities of assignment to treatment groups (urns). Randomization will occur after participants complete the eligibility screening and prior to the manipulation. Variables added to the urn will include both parent (e.g., gender, race/ethnicity, parent substance use) and ASUD characteristics (e.g., number of concerns endorsed on the substance use screener, history of substance use treatment).

Parents will be randomized to one of two conditions: targeted marketing or standard clinical information. Parents in the marketing condition will be presented with the descriptions of EBP that were rated as most appealing in Phase 2, whereas parents in the standard information condition will review descriptions of EBP created for parents by leading scientific organizations in our field such as the National Institute on Drug Abuse (NIDA), Division 53 of The Society of Clinical Child and Adolescent Psychology (APA), and the Substance Abuse and Mental Health Services Administration. A sample standard clinical information message (from the APA Division 53 website) is: *Some treatment approaches have a strong backing in scientific evidence and other treatments have less evidence supporting them. Therapists who use treatments based on science use what is called “evidence-based practice…”* Messages will be balanced to ensure comparable number of words.

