### Data collection and measures

The trial and quantitative data collection will be administered with Ilume software, a program designed for research surveys that is frequently used by the investigative team and that minimizes the likelihood of missing data. *Baseline*. In addition to the core set of measures, parents will answer questions assessing EBP attitudes, awareness, prior use, and intent to use (based on survey items from Phase 2). Parents will then be presented with one of two descriptions of EBP, depending on their random assignment. *Post-intervention*. Parents will complete Likert-scale ratings of the presented information in terms of its relevance to their teen/family, appeal, believability, ease of understanding, and amount of information conveyed. Parents will then complete the PSQ measure and a Behavioral Intentions Scale. After parents complete these measures, they will view a message thanking them for their participation. They will then see two links: 1) a link to end the study session, and 2) a link to receive more information about EBP service options for their teenager. The proportion of parents clicking the link to receive more information will be viewed as a secondary indicator of intentions to seek out EBP.

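### Covariate adjustment in Phase 3 is run only after a positive unadjusted test, so baseline and urn variables cannot add power to the two continuous outcomes

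*Protocol article*

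**What the plan says.** All references are to the Phase 3 sections of the protocol article.

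- **Outcomes, hypothesis tests.** For PSQ: "Mean comparisons will be used to test the hypothesis that participants in the marketing condition will have greater perceptions of service". Behavioral intentions and the information request are tested by group comparisons, one continuous and one categorical. No covariate enters any of the three tests.
- **Outcomes, adjustment.** "If group differences emerge in these basic analyses, multiple regression models will test whether the group differences persist". The covariates named for this step are EBP attitudes, EBP awareness, intentions to seek therapy, and message readability. The list is given as examples.
- **Data collection and measures.** Before exposure, "parents will answer questions assessing EBP attitudes, awareness, prior use, and intent to use".
- **Randomization.** "Variables added to the urn will include both parent (e.g., gender, race/ethnicity, parent substance use) and ASUD characteristics". The teen characteristics named are the count of screener concerns and treatment history.
- **Sample size and power.** "The target sample of 160 (n = 80 per group) will provide 71 percent power to detect an ES of .4", then "88 percent for an ES of .5; and 96 percent for an ES of .6". The average effect cited from prior marketing studies is .20. The one health-care study among them gave .30, and a screening campaign gave .26.

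None of the five named urn variables is named in a hypothesis test or in the conditional regression. Gender, race/ethnicity and treatment history return as exploratory moderators.

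**The concern.** The rule works in one direction. If the unadjusted test is positive, the regression may confirm the difference or take it away. If the unadjusted test is negative, the regression is never run, even where a strong baseline predictor would have sharpened the estimate enough to show a difference.

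Two sources of precision are therefore unused in the tests that decide the hypotheses. One is the set of baseline EBP questions; intent to use is a natural predictor of the Behavioral Intentions Scale. The other is the set of urn variables. When assignment is balanced on a variable that predicts the outcome and the test leaves it out, the standard error is too large for the design, and the test rejects less often than its nominal level.

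This matters because the trial states only 71% power at ES .4, and the effects it cites are smaller than that.

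**Working it through.** **Inputs.** n = 80 per group and the stated power come from Sample size and power. Alpha and sidedness are not stated. R², the share of within-group outcome variance explained by the covariates, is not given and is assumed.

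**Step 1: reproduce the plan's figure.** A two-sample t-test with n per group has noncentrality d·√(n/2) on 2n − 2 = 158 degrees of freedom. For d = .4 this is .4 × √40 = 2.53. At two-sided alpha .05, power is 71.0%, 88.2% and 96.5% at ES .4, .5 and .6, against 71%, 88% and 96% stated. One-sided .05 gives 81%, 93% and 98%, so two-sided .05 is inferred. The power statement thus describes an unadjusted comparison.

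**Step 2: power of a prespecified adjusted test.** Adjustment shrinks the residual SD by √(1 − R²), so d is replaced by d/√(1 − R²). At R² = .25 and d = .4 this is .4/.866 = .462, giving 82.7%.

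| Assumed R² | ES .3 | ES .4 | ES .5 |
|---|---|---|---|
| 0 (unadjusted) | 47% | 71% | 88% |
| .04 | 49% | 73% | 89% |
| .09 | 51% | 75% | 91% |
| .16 | 54% | 78% | 93% |
| .25 | 59% | 83% | 95% |
| .36 | 65% | 88% | 98% |

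**Step 3: simulate the gate.** Each setting used 20,000 trials with 80 per group and one continuous covariate, at ES .4.

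| Assumed R² | Prespecified adjusted test significant | Both tests significant | Adjusted test significant but never run |
|---|---|---|---|
| .09 | 75% | 69% | 6% |
| .25 | 82% | 68% | 14% |

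With no true effect, the prespecified adjusted test rejected in 5.1% and 5.3% of trials.

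**Step 4: leave out balanced urn variables.** In the limit of perfect balance, the true two-sided alpha of the unadjusted test is 2·(1 − Φ(1.96/√(1 − R²))). At R² = .1 this is 2·(1 − Φ(2.066)) = .039. The last two columns are power at ES .4 (normal approximation).

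| Assumed urn R² | True alpha | Unadjusted power | Adjusted power |
|---|---|---|---|
| .1 | .039 | 73% | 76% |
| .2 | .028 | 74% | 81% |
| .3 | .019 | 75% | 86% |

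An urn balances imperfectly, so the actual departure from .05 is smaller than shown.

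**Step 5: message readability.** The conditional model lists it as a pre-manipulation variable, but it belongs to the message and the message is set by assignment. With one message per group it takes one value per group and cannot be separated from arm. With several messages per group it is still largely confounded with arm.

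**Step 6: the binary outcome.** No click rate is given. If 10%, 15% or 30% of 160 parents request information (assumed), there are 16, 24 or 48 events. Attitudes, awareness, intent and five urn variables, one with several categories, come to roughly ten terms. At the lower rates that is too sparse for a logistic model.

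**The case against.** An unadjusted comparison of randomized groups is valid. The power calculation and the planned tests agree with each other, and the study describes itself as proof of concept. The three tests are always run; the regression is a follow-up robustness check, and gating it cannot inflate type I error. The gain may also be small: at R² = .04 or .09 it is 2 or 4 points at ES .4, and at ES .5 power is already 88%. All of this stands, and it limits the point to efficiency.

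Several stronger readings are tempting, and the article does not support them.

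- **That the urn variables are ignored altogether.** Three of the five named are tested as moderators, and the covariate list is open. The statement holds only for the hypothesis tests and the named regression covariates.
- **That recruitment source is wrongly left out.** The urn and covariate lists are both given as examples, so its absence is not shown, and its effect on requesting information is conjecture.
- **That checking whether a difference survives adjustment is invalid for the binary outcome, because odds ratios change on adjustment.** No odds ratio is named and no comparison of effect sizes is planned. That property also does not create an effect where there is none.
- **That every outcome has a baseline counterpart.** Intent is one for the Behavioral Intentions Scale. PSQ is measured only after the message.

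The objection does not rescue the condition itself. It is a decision rule stated in the article, not a detail left to a fuller document, and it gives up precision from data the trial collects anyway.

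**Conclusion.** The concern holds as a loss of efficiency for the two continuous outcomes. The unadjusted tests are valid and, where the urn variables predict the outcome, somewhat conservative. The conditional rule means adjustment can only take findings away.

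The size depends on an R² that the article does not give. Over the assumed range of .04 to .36, the gain is 2 to 17 points at ES .4 (71% to 73–88%) and 2 to 18 points at ES .3 (47% to 49–65%). The alpha values of .039, .028 and .019 are perfect-balance limits at assumed urn R² of .1, .2 and .3. All figures assume two-sided alpha .05. No gain was computed for the information request, and none is claimed.

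**What to change.** Reword the Outcomes section as follows.

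- **PSQ and Behavioral Intentions Scale.** The primary test is one prespecified linear model per outcome on arm, baseline EBP attitudes, awareness and intent, and the urn variables. Run it whatever the unadjusted comparison shows, and report the unadjusted comparison alongside.
- **Message readability.** Leave it out of this model. It can be reported descriptively for each message.
- **Information request.** Keep the unadjusted comparison of proportions as the main test. Add a prespecified adjusted analysis with a short covariate list, such as baseline intent, run regardless of the unadjusted result and reported as a risk difference.

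The baseline and urn data are already planned for every parent. The cost is the change of wording and a few degrees of freedom out of 158.

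### The follow-up regression lists message readability as a pre-manipulation covariate, but readability is set by the arm, so with one text or set of texts per arm the adjusted group effect cannot be estimated

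*Protocol article*

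**What the plan says.** The Outcomes section of the protocol article tests the Phase 3 hypotheses first by unadjusted comparison. For perceived service quality (PSQ): "Mean comparisons will be used to test the hypothesis that participants in the marketing condition will have greater perceptions of service". Behavioral intentions and information requests are likewise compared directly between groups.

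A second step is conditional: "If group differences emerge in these basic analyses, multiple regression models will test whether the group differences persist". The adjustment made in this second step is described, with its example covariates, as "controlling for pre-manipulation variables such as EBP attitudes, EBP awareness, intentions to seek therapy, and readability statistics generated on the messages".

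Three other statements bear on whether that second step can work:

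- Data collection and measures: "Parents will then be presented with one of two descriptions of EBP, depending on their random assignment".
- Randomization, marketing arm: "Parents in the marketing condition will be presented with the descriptions of EBP that were rated as most appealing in Phase 2". Control arm: "parents in the standard information condition will review descriptions of EBP created for parents by leading scientific organizations in our field". Both use the plural, but neither describes parents within an arm being given different texts.
- Randomization, on matching the texts: "Messages will be balanced to ensure comparable number of words". Word count is the only feature named.

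Outcomes also plans an exploratory analysis in which "ratings of the information (e.g., ease of understanding, believability) will be tested as potential mediators of outcome".

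**The concern.** A covariate in a model for a randomized group effect should describe the participant before the intervention. EBP attitudes, awareness and intentions do, since they are asked at baseline. A readability score computed on a message does not: it describes what the parent was randomized to read. Calling it pre-manipulation misclassifies part of the intervention as a baseline variable.

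Two consequences are possible. If the score takes one value per arm, it carries the same information as the group indicator and the model cannot separate them. If it varies within arm, the model runs, but its group coefficient answers a different question: the effect of the message with readability held fixed. That sits badly with the article's own treatment of ease of understanding as a possible mediator, that is, as something on the path from message to outcome.

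At stake is the statement that a difference does or does not persist after adjustment. This is the only adjusted analysis of the group effect that the article describes, and it stands apart from the analyses labelled exploratory.

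**Working it through.** **Inputs.** From Sample size and power: N = 160, 80 per group, power 71%, 88% and 96% at effect sizes 0.4, 0.5 and 0.6. From Outcomes: group and readability in the same model. From Data collection and measures: one of two descriptions, fixed by arm. Assumed because not stated: two-sided alpha 0.05, and all readability values used below.

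**Step 1. The plan's own figures.** For two means with 80 per group, in SD units, SE = √(2/80) = 0.158 and power ≈ Φ(ES/SE − 1.96).

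| ES | Stated | Normal approximation | Noncentral t |
|---|---|---|---|
| 0.4 | 71% | 71.6% | 71.0% |
| 0.5 | 88% | 88.5% | 88.2% |
| 0.6 | 96% | 96.7% | 96.5% |

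The stated power is reproduced. It belongs to the unadjusted comparison and does not involve readability.

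**Step 2. Same text or set of texts for everyone in an arm.** Let the readability score be R0 in the control arm and R1 in the marketing arm. Every parent then has R = R0 + (R1 − R0) × arm. Put this into the regression:

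Y = b0 + b1·arm + b2·R = (b0 + b2·R0) + [b1 + b2·(R1 − R0)]·arm

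The data determine only the two bracketed quantities, so b1 and b2 cannot be separated. Numerical check with 80 parents per arm and illustrative scores of 12 and 7: the matrix [1, arm, R] has rank 2 for 3 columns. The same holds for any readability index, and for each outcome, because the defect is in the design matrix. More participants would not help. If R0 = R1, readability is a constant and adds nothing to the model.

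**Step 3. Different texts for different parents within an arm.** The article does not describe this, so the following is purely illustrative: three texts per arm, readability in grade levels, VIF = 1/(1 − r²) with r the correlation of arm and readability, SE = 0.158 × √VIF, and power at ES 0.5.

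| Gap between arms (grades) | Within-arm SD | VIF | Power at ES 0.5 |
|---|---|---|---|
| 5 | 0.5 | 25.9 | 9% |
| 5 | 1 | 7.2 | 22% |
| 5 | 2 | 2.5 | 51% |
| 3 | 1 | 3.2 | 42% |
| 3 | 2 | 1.6 | 72% |
| 0 | 2 | 1.0 | 88% |

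For the second row: SE = 0.158 × √7.19 = 0.424, and Φ(0.5/0.424 − 1.96) = Φ(−0.78) = 22%. These figures show loss of precision only. They keep the effect at 0.5, whereas the adjusted coefficient would also leave out whatever part of the effect runs through readability.

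**The case against.** The strongest reply is that little depends on this regression. All three hypotheses are tested by unadjusted group comparisons, and the regression is reached only if those show a difference. That is correct. A reader might infer that the trial's main tests are compromised, or that this is the confirmatory model; the article supports neither reading.

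Second, the plural in Randomization leaves some room for several texts per arm, so perfect collinearity is conditional. This stands in part. But a set of texts shown to everyone in an arm still yields one score per arm, and no allocation of different texts to different parents is described. The sentence in Data collection and measures points the other way.

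Third, even with several texts the terms need not be close to collinear. This stands. The illustrative VIFs run from 1.0 to 25.9, and with no readability gap nothing is lost. The article gives no gap, so near-collinearity should not be asserted.

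Fourth, a singular model usually announces itself: software stops or drops a term. That limits the harm but does not remove it. If the group term is the one dropped, the arm contrast appears under the name of readability.

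Finally, the covariates are introduced as examples. Readability is nevertheless named among them.

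**Conclusion.** The point holds as a defect in one named covariate of a conditional follow-up model. Readability is not a pre-manipulation variable. If all parents in an arm see the same text or set of texts, which is what the article indicates, intercept, arm and readability have rank 2 of 3, and the model cannot say whether the group difference persists. If texts varied between parents within an arm, the model could be fitted, with a loss of precision that the article's figures do not fix and with a changed meaning of the group effect.

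A reader might also infer that adjustment would remove the whole intervention effect. That would follow only if the effect ran entirely through readability, and nothing in the article says so; otherwise the removal is partial.

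The unadjusted tests, the power statement and the other three named covariates are unaffected. Should be fixed.

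**What to change.** Delete the reference to message readability statistics from the covariate list in Outcomes. Keep EBP attitudes, EBP awareness and intentions, which are genuine baseline covariates. Report the readability score of each arm's text or texts descriptively, as a feature of the intervention. Keep parents' ease-of-understanding rating where it already is, as an exploratory mediator.

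Matching the two descriptions on reading level, alongside word count, is optional. It is a design choice rather than a consequence of the error: plain wording drawn from parents' own comments may be part of what the marketing message is meant to offer. If matching is wanted, it has to be done before the texts are final.

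The cost is one deleted phrase and two reported scores, with no added participants or data collection.

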## Discussion

The current study addresses an issue of importance to our field and our nation’s public health: increasing the utilization of EBP by ASUDs. While prior studies have worked to increase the utilization of EBP by targeting treatment providers, this study evaluates the relevance of DTC marketing to deliver information directly to parents of ASUDs. Qualitative data collection from ASUDs and their parents will be used to evaluate the utility of the Marketing Mix framework in developing targeted messages and to develop a new measure of PSQ, a key construct in predicting demand for a service. A subsequent targeted survey will be used to further evaluate the Marketing Mix and to validate the PSQ measure. The final phase of the study will test the hypotheses that targeted marketing messages developed using the Marketing Mix framework, which will be associated with greater perceptions of service quality (using the PSQ measure) and greater behavioral intentions to seek out information about EBP than standard clinical information. Results of this study will have the potential to immediately inform DTC marketing efforts by professional organizations, federal agencies, clinicians, and clinical researchers.

## Abbreviations

APA: American psychological association
ASUD: Adolescent substance use disorder
ASUDs: Adolescents with substance use disorders
D&I: Dissemination and implementation
DTC: Direct-to-consumer
EBP: Evidence-based practice
ES: Effect size
PSQ: Perceived service quality
